#### Nigeria

The intervention will be evaluated in Ogun (South Nigeria) and Nasarawa (North Nigeria) through population-based surveys conducted at baseline (late 2017) and approximately 24 months after the start of the intervention. In Nasarawa, four LGAs consisting of two similar pairs have been selected for evaluation. Two of these will receive the intervention (one in each pair) and two will not, that is, they will act as comparisons. In Ogun, the evaluation will be conducted in only two LGAs (one intervention and one comparison).

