##### Study unit inclusion criteria and selection

Study states were selected by SFH. The selected states were chosen because of the absence of other large-scale adolescent focused sexual and reproductive health activities and because of SFH’s previous experience working in these states.

Study LGAs were selected by SFH in collaboration with the state Ministry of Health and local government officials. The LGAs were selected from among those where there were no security concerns, and comparison-intervention pairs were selected to be similar with respect to as many as possible of the following criteria:Population density.Estimated modern contraceptive prevalence rate (mCPR) among 15–49 year olds (DHIS2, 2016).^17^
Number of health facilities.Presence of World Bank support for Maternal and Child Health activities.

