##### Allocation to intervention and comparison arms

Within a pair, allocation of an LGA to the intervention or comparison arm of the outcome evaluation study was done by SFH in collaboration with the state Ministry of Health and local government officials.

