### Data analysis

In Nigeria, our hypothesis is that sexually active girls aged 15–19 years living in areas where the A360 programme is implemented will have a greater increase in use of modern contraception compared with sexually active girls aged 15–19 years living in areas where the A360 programme has not been implemented. We will estimate the intervention effect separately for Ogun and each LGA-pair in Nasarawa. The effect estimates will be obtained by subtracting the baseline mCPR prevalence estimates from the prevalence estimates at follow-up and then calculating the difference between the comparison and intervention LGAs (the difference in difference method). If the two effect estimates for Nasarawa are similar, then we will combine them (eg, by weighting by the inverse of the variance) to produce a single summary estimate for the state. Similar analyses will be performed to look at the intervention effect on secondary outcomes (table 3). The difference in differences analysis assumes a common trend in the outcome in both the intervention and comparison area. Even if the two areas differ in a number of characteristics, the analysis is valid provided the common trend assumption is upheld. We will measure potential confounders at baseline and endline and adjust our analysis for any compositional changes over time in these confounders.

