
All analyses will be conducted in Stata V.15 and we will use weights and robust SEs to account for the cluster sampling design.

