### Strengths and limitations

A strength of our outcome evaluation is the collection of comparable data before and after intervention implementation in four different settings in three countries. In two settings in Nigeria, we will also collect data from populations not exposed to the intervention and hence will have a quasi-experimental design.^45^ Triangulation with dose–response and trends analyses and implementer monitoring and evaluation data will strengthen the inference possible from the study findings. A process evaluation, conducted throughout the 2-year implementation period in the outcome evaluation areas, will provide information on the context and mechanism of the intervention and will complement the outcome data.

In Nigeria, where the intervention will be evaluated through a quasi-experimental design, the validity of the effect estimate depends on the time trend being the same in both intervention and comparison areas. The common trend assumption is untestable because we will not know what the trend in the intervention area would have been in the absence of the intervention. We have tried to select LGAs with similar key sociodemographic and reproductive health indicators as trends in mCPR are likely to be influenced by the characteristics of the population. In addition, our baseline survey will allow us to undertake a more accurate assessment as to how comparable our study sites are on a number of additional key indicators and we will be able to adjust for imbalances in potential confounders at the analysis stage.

In Tanzania and Ethiopia, the study design does not include a comparison group and observed changes in mCPR could be due to secular trends or other influences. As described above, we will examine historical and contemporaneous mCPR data from other sources so that our findings can be interpreted in the context of underlying trends. In addition, a dose–response analysis will be conducted at endline to look at the association between individual-level engagement with the A360 intervention and modern contraception use.

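### Nigeria: one LGA per arm in Ogun and in each Nasarawa pair, but the planned standard errors cover only EA sampling within LGAs, so the intervals hold only under an exactly common trend

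*Protocol article*

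**What the plan says.** All references are to the Protocol article.

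- **Design of outcome evaluation, Nigeria:** "In Ogun, the evaluation will be conducted in only two LGAs (one intervention and one comparison"). Of the four Nasarawa LGAs, "Two of these will receive the intervention (one in each pair) and two will not, that is, they will act as comparisons".
- **Nigeria, section on allocation to arms:** for each pair the article states that "allocation of an LGA to the intervention or comparison arm of the outcome evaluation study was done by SFH", together with state and local officials.
- **Data analysis:** "We will estimate the intervention effect separately for Ogun and each LGA-pair in Nasarawa", by difference in differences. For pooling: "If the two effect estimates for Nasarawa are similar, then we will combine them (eg, by weighting by the inverse of the variance"). The closing sentence, which covers all analyses, says "we will use weights and robust SEs to account for the cluster sampling design".
- **Sampling strategy and Table 2:** the primary sampling unit in Nigeria is the EA.
- **Strengths and limitations:** "The common trend assumption is untestable because we will not know what the trend in the intervention area would have been in the absence of" A360. The same paragraph points to the choice of similar LGAs, a baseline check of comparability and adjustment for imbalances.
- **Study unit inclusion criteria and selection (Nigeria):** one of the matching criteria was "Estimated modern contraceptive prevalence rate (mCPR) among 15–49 year olds (DHIS2, 2016").
- **Data analysis, secular trends:** this check is described under Ethiopia and Tanzania, and its named data sources come from those two countries.

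**The concern.** The unit that receives A360 is the LGA. With one LGA per arm, anything specific to one LGA over 24 months (a stock-out, a change in facilities, another programme) cannot be separated from A360. EA-level robust errors measure how precisely each LGA's prevalence is known at each round. They do not measure how far two LGAs would drift apart without any intervention.

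In Ogun that drift cannot be estimated from the pair itself, so no choice of standard error within Ogun repairs the interval. In Nasarawa the two pairs leave one degree of freedom for it. Inverse-variance pooling only when the two estimates look similar then leaves that variation out of the pooled variance.

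The Nigerian comparison is the only concurrently controlled contrast in the study. If its interval is too narrow, the false-positive rate is above the nominal level and the finding looks firmer than two or four LGAs can support. The article says the evaluation was meant to detect small increases, so modest drift matters.

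**Working it through.** **1. Reproduce the sample size targets.** Inputs are the assumed prevalences in the Sample size section. Ogun: 64.4% to 65.6% without A360 and 64.4% to 72.6% with it, a difference in differences of 7.0 points. Nasarawa: 3.0% to 3.1% and 3.0% to 5.1%, a difference of 2.0 points. Two-sided 5% is assumed, since no alpha is stated.

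n per arm per round = (z_α/2 + z_β)² × Σp(1−p) / d², summed over the four arm-by-round cells.

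- Ogun: Σp(1−p) = 0.8831; (1.96 + 0.84)² × 0.8831 / 0.07² = **1413**, as in Table 5. This corresponds to 80% power; the article states no power for Ogun.
- Nasarawa: Σp(1−p) = 0.1366; (1.96 + 1.28)² × 0.1366 / 0.02² = **3586**, as in Table 5, at the stated 90% power.
- Remaining rows: 1413 / 0.15 × 1.1 = 10 362, × 1.16 = 12 020; 3586 / 0.97 × 1.1 = 4067, × 1.12 = 4555.

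The variance is binomial within cells, and the design effect is the only clustering allowance. There is no LGA-level term.

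**2. Standard error as planned, with no true effect.** Because the survey size is inflated by the design effect, the Table 5 targets serve as effective sizes. The formula gives 1413 and 3586 per arm per round, but Table 2 and the Sampling strategy read as if the survey sizes were state totals. Both readings are shown. The cells are 64.4% and 65.6% in both Ogun arms (Σp(1−p) = 0.9099), and 3.0% and 3.1% in both Nasarawa arms (0.1183).

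- Ogun, 1413 shared (706.5 per cell): √(0.9099 / 706.5) = 3.59 points. With 1413 per cell: 2.54 points.
- Nasarawa pooled, 3586 shared (1793 per cell): 0.81 points. With 3586 per cell: 0.57 points.

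**3. Add the LGA trend SD, τ.** τ is the SD of an LGA's own 24-month change. It is not in the article, so a range is assumed. One pair adds τ² from each LGA, so total SE² = SE² + 2τ². The mean of two pairs adds (2τ² + 2τ²)/4 = τ². The true rejection rate of the nominal 5% test is 2(1 − Φ(1.96 × SE / total SE)).

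| Setting | τ (points) | Target shared between arms | Target per arm per round |
|---|---|---|---|
| Ogun (planned effect 7.0) | 1 | 6.8% | 8.7% |
| | 2 | 12.4% | 19.1% |
| | 3 | 20.6% | 31.4% |
| Nasarawa pooled (planned effect 2.0) | 0.25 | 6.1% | 7.2% |
| | 0.5 | 9.5% | 13.9% |
| | 1.0 | 21.7% | 32.9% |

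Worked line, Ogun at τ = 2 with 1413 per cell: total SE = √(2.54² + 2 × 2²) = 3.80. The 95% half-width should be 7.5 points, not 5.0, and 1.96 × 2.54 / 3.80 = 1.31 gives 19.1%.

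**4. What the study's own data can show.** Toto and Nasarawa LGAs are both untreated and both surveyed at the two rounds. The difference between their changes is one direct observation of drift between untreated LGAs, in the target population and on the study outcome.

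**The case against.** The strongest reply is that the threat is disclosed and partly handled. LGAs were matched on several criteria, and states were chosen for the absence of other large adolescent programmes. Confounders are measured at both rounds and adjusted for. A process evaluation runs throughout in the evaluation areas. The article also says that causal conclusions are less definitive than from a cluster-randomised design. Robust errors for the sampling design are correct for that purpose, and sensitivity analyses often sit in an analysis plan or in the separate country protocols.

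Most of this stands, and it rules out several stronger readings that a reader might infer:

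- **That LGA drift will be reported as an A360 effect.** The article gives no LGA trend SD; if drift is negligible, the interval is nearly right. Only that it can be so reported is supported.
- **That the protocol names the assumption and does nothing.** Matching, adjustment and process evaluation are planned.
- **That the planned data say nothing about drift between untreated LGAs.** Nasarawa supplies one such contrast, and the two pair estimates give a crude check on each other.
- **That an LGA-level DHIS2 trend series is already in hand.** The article cites a single 2016 estimate for ages 15–49, used in matching.

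The core is not answered. Matching may reduce drift, and adjustment for composition deals with who lives in the LGA; neither adds the remaining LGA-specific variation to the variance. The limitation about randomisation does not cover it either, because randomising two LGAs would still leave one per arm. Nor is this only a detail left to another document: the article itself fixes the standard-error method for all analyses and nowhere says that the interval leaves this variation out.

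**Conclusion.** The point holds in a bounded form. The Nigerian intervals and p-values are valid only under an exactly common trend; with any LGA-level variation in trend they are too narrow. Under the assumed SDs, the true rejection rate of a nominal 5% test is about 7–21% in Ogun (9–31% on the per-arm-per-round reading) and about 6–22% in Nasarawa (7–33%).

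These figures rest on assumed SDs of 1–3 and 0.25–1.0 points, independent LGA changes with equal SD, equal weighting of the Nasarawa pairs and a two-sided 5% test. The direction of the error does not depend on the SD chosen; its size does. The point estimate can stand as planned. What needs correcting is the certainty attached to it.

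**What to change.** Before the endline analysis:

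1. State beside each Nigerian estimate that its interval is conditional on a common trend and covers within-LGA sampling only.
2. Prespecify a sensitivity analysis that adds 2τ² to the variance for one pair, or τ² for two pooled pairs, over a stated range of LGA trend SDs. Report the trend difference that would remove the effect.
3. Report the difference in change between the two untreated Nasarawa LGAs as one direct benchmark. Show the two pair estimates side by side whether or not they are pooled.
4. If an LGA-level DHIS2 series proves available and usable, compare pre-A360 trends within pairs and show the spread across untreated LGAs. Treat this as a rough benchmark only: it would cover ages 15–49, and LGAs that were not matched.

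Steps 1 to 3 need no new data, only wording and short calculations. Step 4 depends on access to the series and on its quality. The cost is a less favourable statement of certainty for the Nigerian results.

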### Sample size

The baseline mCPR estimates and projected trends used in our sample size calculations were based on analysis which PSI conducted in September 2015 using available DHS data and our own review of historical DHS and PMA2020 data.^7 18 24 25^

Effect estimates are based on an analysis (unpublish ed) conducted by one of our evaluation collaborators, [name] (Avenir Health). She reviewed 25 studies published between 1993 and 2014, which had estimated the impact of family planning interventions on mCPR using a variety of study designs.^26–44^ [name] extracted published ORs for effect size when available or calculated them using published results. She then calculated the median and maximum ORs to give a sense of the average and maximum increase in mCPR expected based on the existing evidence base.

#### Nigeria

In Ogun State, among sexually active unmarried girls aged 15–19 years, we assumed that between 2017 and 2019, mCPR will increase from 64.4% to 65.6% in the absence of A360 and from 64.4% to 72.6% in the presence of A360. Based on these assumptions and those in tables 4 and 5, our target sample size is 12 020 unmarried girls aged 15–19 years.

**Table 4 T4:** Assumptions for key parameters required for sample size calculations

Parameter	Ogun* (%)	Nasarawa* (%)	Oromia† (%)	Mwanza‡ (%)
Proportion of 15–19-year-old girls who are married (or living together)	10	15	20	22
Proportion of 15–19-year-old girls who are unmarried (not currently married)	90	85	80	78
Proportion of unmarried 15–19-year-old girls who report sexual activity in the past year	15	15	–	25
Proportion of married 15–19 year olds who report sexual activity in the past year	97	97	97	97
Proportion of sexually active girls who are married	42	53	–	52
Proportion of sexually active girls who are unmarried	58	47	–	48
Proportion of households with resident who is female aged 15–19 years	19	29	27	34

Sources:

*Nigeria DHS 2013,^7^ Nigeria GHS 2016.^13^

†Ethiopia DHS 2011,^18^ Ethiopia Mini DHS 2014,^24^ Ethiopia census 2007.^14^

‡Tanzania DHS 2015–2016,^9^ Tanzania census 2012.^15^

DHS, Demographic and Health Survey.

**Table 5 T5:** Sample size estimates

Parameter	Ogun	Nasarawa	Oromia	Mwanza
Target sample of sexually active 15–19 year olds*	1413	3586	1132	1217
Total sample of all 15–19 year olds* Includes non-sexually active girls Taking into account 10% non-response	10 362	4067	1284	3314
Design effect	1.16	1.12	1.50	1.50
Sample size for survey†	12 020	4555	1926	4980

*Includes unmarried girls (Ogun); married girls (Nasarawa and Ethiopia); unmarried and married girls (Mwanza).

†Total sample of all 15–19 year olds × design effect.

In Nasarawa State, among sexually active married 15–19 year olds, we have assumed that between 2017 and 2019, mCPR will increase from 3.0% to 3.1% in the absence of A360 and from 3.0% to 5.1% in the presence of A360. Thus, 4555 married girls aged 15–19 years must be surveyed to achieve 90% power (table 5).

In addition, a sample of 250 cohabiting adults (Ogun) and 250 husbands/male partners (Nasarawa) will be interviewed.

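### Table 5 adds 10% for non-response in Ogun, Nasarawa and Oromia where a 10% loss requires division by 0.9, so these three survey sizes yield 99% of their own targets

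*Protocol article*

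**What the plan says.** Table 5 (Sample size section, under Nigeria) builds each survey size in three steps. It starts from a "Target sample of sexually active 15–19 year olds": 1413 in Ogun, 3586 in Nasarawa, 1132 in Oromia and 1217 in Mwanza. The next row converts this to all girls of that age in the study population. Its label says that it covers girls who are not sexually active and adds "Taking into account 10% non-response"; it reads 10 362, 4067, 1284 and 3314. The last row is defined in the footnote as "Total sample of all 15–19 year olds × design effect". With design effects of 1.16, 1.12, 1.50 and 1.50 it gives 12 020, 4555, 1926 and 4980.

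The label on the middle row is the same for all four sites, and the article does not print the inflation formula. The text ties the final sizes to power. For Nasarawa it says that "4555 married girls aged 15–19 years must be surveyed to achieve 90% power", and it makes the same 90% statement for 1926 girls in Oromia and 4980 in Mwanza. For Ogun it gives a target sample size but no power.

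**The concern.** A non-response rate is a share lost from those approached. To end with n respondents when 10% are lost, n/0.9 must be approached. Adding 10% to n gives 1.1n, of which 90% respond, leaving 0.99n. Three of the four totals in Table 5 match the second calculation. At the plan's own non-response rate those survey sizes therefore do not deliver the targets printed in the same table, and the 90% power attached to two of them is slightly too high. The Sample size section says the evaluation was meant to be powered for small increases, so the inputs and outputs of the calculation ought to agree.

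**Working it through.** **Inputs.** Targets, totals, design effects and survey sizes are from Table 5. The share of girls sexually active in the past year is from Table 4: 15% of unmarried girls in Ogun, and 97% of married girls in Nasarawa and Oromia. Mwanza covers both groups: 22% married with 97% active, and 78% unmarried with 25% active.

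**Step 1: reproduce the printed totals (target / active share × allowance).**

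| Site | Target / share | × 1.1 | / 0.9 | Printed |
|---|---|---|---|---|
| Ogun | 1413/0.15 = 9420.0 | 10 362.0 | 10 466.7 | 10 362 |
| Nasarawa | 3586/0.97 = 3696.9 | 4066.6 | 4107.7 | 4067 |
| Oromia | 1132/0.97 = 1167.0 | 1283.7 | 1296.7 | 1284 |

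Multiplication by 1.1 matches all three to the unit. Multiplying the printed totals by the design effects returns the printed survey sizes: 10 362 × 1.16 = 12 020, 4067 × 1.12 = 4555 and 1284 × 1.50 = 1926.

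**Step 2: expected yield at 10% non-response, net of design effect (printed total × 0.9 × active share).**

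- Ogun: 10 362 × 0.9 × 0.15 = 1399 against 1413 (14 short).
- Nasarawa: 4067 × 0.9 × 0.97 = 3550 against 3586 (36 short).
- Oromia: 1284 × 0.9 × 0.97 = 1121 against 1132 (11 short).

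Each is 1% short, as 1 − 1.1 × 0.9 implies. This step uses only printed figures, so it does not depend on which formula the authors used.

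**Step 3: sizes with division by 0.9, totals rounded up.**

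- Ogun: 10 467 × 1.16 = 12 142 (stated 12 020, 122 fewer).
- Nasarawa: 4108 × 1.12 = 4601 (stated 4555, 46 fewer).
- Oromia: 1297 × 1.50 = 1946 (stated 1926, 20 fewer).

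**Step 4: power.** For Oromia, comparing 44.0% with 50.8% at a two-sided 5% level (assumed; no level is printed in the article), the standard two-proportion formula without continuity correction gives 1132 per survey for 90% power, which matches Table 5. Cutting that number by 1% takes power from 90.0% to 89.7%. For Nasarawa the target comes from a calculation whose details are in a supplement not shown, so I took the stated 90% as given. Scaling the standardised effect by √0.99 gives (1.960 + 1.282) × 0.995 − 1.960 ≈ 1.265, which is 89.7%.

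**Step 5: Mwanza.** The active share is 0.22 × 0.97 + 0.78 × 0.25 = 0.4084. The stated survey size yields 4980 × 0.9 × 0.4084 / 1.5 = 1220 against a target of 1217, so it is met. The printed total of 3314 does not identify the formula:

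- With the share at 0.4084, 1217/0.4084 = 2979.9. Division by 0.9 gives 3311 and multiplication by 1.1 gives 3278; neither is 3314.
- With the share rounded first to 0.408, division by 0.9 gives 3314 and multiplication by 1.1 gives 3281.
- With 21.7% married and 24.7% of unmarried girls active, both of which round to the printed 22% and 25%, the share is 0.217 × 0.97 + 0.783 × 0.247 = 0.4039. Then 1217/0.4039 × 1.1 is about 3314.

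Also, 3314 × 1.50 = 4971, not 4980. The printed 4980 equals 30 streets × 166 girls, the per-street number in the Sampling strategy section for Tanzania, which points to rounding up by street (4971/30 = 165.7).

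**The case against.** A reader might infer that Table 5 applies one allowance by two formulas: multiplication by 1.1 at three sites and division by 0.9 in Mwanza. Division is the closer fit to the printed Mwanza inputs, but it gives exactly 3314 only if the active share is first rounded to 0.408. Unrounded inputs compatible with Table 4 let multiplication by 1.1 reach the same figure. The article prints no formula and refers to a supplementary file for the details. The documents therefore do not support a claim of two formulas.

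The strongest case against the narrower point is that adding 10% is a common planning convention, that the row label does not promise division by 0.9, and that a 1% difference is lost in the other uncertainties. Much of the last part stands. In Ogun an active share of 15.15% instead of 15% would remove the whole shortfall, and the Sampling strategy section openly says that share is uncertain. Fieldwork takes all eligible girls in roughly 710 and 1150 enumeration areas and in 45 whole kebeles, so it cannot be steered to within 1%. Also, 89.7% rounds to 90%.

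The convention argument does not remove the point. The label names a non-response rate, and no reading of the supplement can make 10 362 × 0.9 × 0.15 equal 1413.

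**Conclusion.** The point holds for Ogun, Nasarawa and Oromia. At the stated 10% non-response, the survey sizes deliver 99% of the targets printed in the same table. The power cost is about 0.3 percentage points where 90% is stated (Nasarawa and Oromia). No loss from a stated power can be claimed for Ogun, because none is stated there. Mwanza is not short.

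This rests on three assumptions: that the survey sizes count girls approached, including those who do not respond, as the Table 5 label implies; that the Table 4 shares are taken as printed; and, for the power figures, a two-sided 5% level and the stated 90% in Nasarawa. It is a small arithmetic slip in stated sample sizes. No design or analysis decision depends on it.

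**What to change.** Either of two changes is enough.

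1. Keep the field sizes of 12 020, 4555 and 1926. State that at 10% non-response they are expected to yield 1399, 3550 and 1121 sexually active girls net of the design effect, with about 89.7% power in Nasarawa and Oromia. This has no field cost and is the simpler choice.
2. Use division by 0.9 for the three sites. The Table 5 totals become 10 467, 4108 and 1297, and the survey sizes about 12 142, 4601 and 1946. The survey sizes also stand in Table 2 and in the Sample size text, so twelve printed figures change (three totals, and three survey sizes in three places each). The approximate numbers of enumeration areas for Ogun and Nasarawa, which were set to reach the present targets, would need a check. The field cost is about 1% more girls at each site.

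In both cases, print the inflation formula under Table 5, and add a note that the Mwanza size of 4980 is 30 streets × 166 girls, since the footnote's multiplication gives 4971.

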### Design of outcome evaluation

A summary of the methods used can be found in table 2. Separate protocols were developed for each country to take into account the country-specific A360 implementation strategies and study designs developed.

**Table 2 T2:** Summary of methods

A360 country	A360 regions	Study design	Outcome evaluation study setting	Study population (sample size)	Sampling strategy
Nigeria (South)	Lagos, Osun, *Ogun*, Oyo, Edo, Delta, Akwa Ibom	Cross-sectional before-and-after study with comparison group	Ogun State: Ado-Odo Ota LGA (intervention) Shagamu LGA (comparison)	Unmarried girls aged 15–19 years (12 020) Cohabiting adults (250)	Single stage cluster design PSU: EA Simple random sample of EAs (approx. 710 in Ogun). All HHs visited in selected EAs. All eligible individuals to be recruited to participate.
Nigeria (North)	Federal Capital Territory, Kaduna, *Nasarawa*	Cross-sectional before-and-after study with comparison group	Nasarawa State: Doma LGA (intervention) Toto LGA (comparison) Karu LGA (intervention) Nasarawa LGA (comparison)	Married girls aged 15–19 years (4555) Husband (250)	Single stage cluster design PSU: EA Simple random sample of EAs (approx. 1150 in Nasarawa). All HHs visited in selected EAs. All eligible individuals to be recruited to participate.
Ethiopia	Addis Ababa, Amhara, Dire Dawa, Harari, *Oromia*, SNNP, Tigray	Cross-sectional before-and-after study	Oromia regional state: Wara Jarso, Lome, Ada’a, Fentale woredas	Married girls aged 15–19 years (1926) Husband (128)	Single stage cluster design PSU: Kebele Probability proportional to size sample of 45 kebele. All HHs visited in selected kebele. All eligible individuals to be recruited to participate.
Tanzania	Kagera, Geita, *Mwanza*, Arusha, Tabora, Tanga, Dar es Salaam, Mbeya, Iringa, Morogoro	Cross-sectional before-and-after study	Mwanza region: Ilemela district (urban and semiurban wards only)	Married and unmarried girls aged 15–19 years (4980) Cohabiting adults (127)	Two stage cluster design PSU: Street Simple random sample of 30 streets. Simple random sample of 50 GPS points within each street. All HHs with front door within 20 m radius of GPS point visited. All eligible individuals recruited to participate.

A360, Adolescents 360; EA, enumerations area; GPS, Global Positioning System; HH, household; LGA, local government area; PSU, primary sampling unit; SNNP, Southern Nations, Nationalities and People’s Region.

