#### Nigeria

The Nigeria Population Commission maintains a database of about 600 000 EAs across the entire country, which shows that EAs in Nasarawa have an average of 44 households and EAs in Ogun have an average of 52 households. They advised us that EA population counts are considered unreliable, which creates issues when using proportional to population size sampling techniques. To overcome this issue, we will use a simple random sample of EAs. To maximise the efficiency, in terms of logistics, of the study, we will sample clusters of approximately 100 households. Thus, if a selected EA contains fewer than 100 households, then we will randomly sample one of the neighbouring EAs and enumerate all households in that EA. If 100 households are still not enumerated, then a further additional EA will be randomly sampled and enumerated. We estimate that, using this technique, a simple random sample of approximately 710 EAs in Ogun and 1150 EAs in Nasarawa will need to be selected to reach the target sample size of adolescent girls. All eligible unmarried girls aged 15–19 years in the selected households in Ogun and all eligible married girls aged 15–19 years in Nasarawa will be recruited to participate in the structured interview. In Nasarawa, in order to reach our target sample size of 250 husbands, we estimated that for every 17 sexually active married girls interviewed, one will be systematically selected and asked permission to interview her husband. In Ogun, due to the uncertainty in the proportion of unmarried girls who will report that they are sexually active, we propose that for every 7–14 sexually active unmarried girls surveyed, one will be systematically selected and asked permission to interview a cohabiting adult in order to reach our target sample size of 250 cohabiting adults. The exact sampling interval will be finalised following the pilot study.

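### Nasarawa's 4555 girls is a per-arm, per-round requirement that the protocol uses as the total for four LGAs; as a total it gives about 63% power, not 90%, and Ogun has the same mismatch

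*Protocol article*

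**What the plan says.** The Data analysis section makes the Nigerian effect estimate a change from baseline to follow-up, contrasted between arms by "calculating the difference between the comparison and intervention LGAs (the difference in difference method". It is estimated separately for Ogun and for each of the two LGA pairs in Nasarawa. The Nasarawa pairs are combined only if their estimates are similar.

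The Sample size section, under Nigeria, assumes for Nasarawa that "mCPR will increase from 3.0% to 3.1% in the absence of A360 and from 3.0% to 5.1% in the presence of A360", and for Ogun that "mCPR will increase from 64.4% to 65.6% in the absence of A360 and from 64.4% to 72.6% in the presence of A360". It concludes for Nasarawa: "Thus, 4555 married girls aged 15–19 years must be surveyed to achieve 90% power (table 5". It gives no power for Ogun, and no alpha anywhere.

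The Table 5 row headed "Target sample of sexually active 15–19 year olds" shows 3586 for Nasarawa and 1413 for Ogun. These become 4555 and 12 020 after allowance for sexual activity, non-response and design effect. The table does not say whether its figures are per arm, per round or in total.

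Table 2 gives one sample size per setting: 4555 against four named Nasarawa LGAs (two intervention, two comparison) and 12 020 against two named Ogun LGAs. Its sampling column reads "Simple random sample of EAs (approx. 1150 in Nasarawa", with about 710 for Ogun. To obtain 250 husbands in Nasarawa, the Sampling strategy section says that "for every 17 sexually active married girls interviewed, one will be systematically selected and asked permission to interview her husband".

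**The concern.** A difference in differences of proportions has four cells: two arms at two rounds. A sample size formula for it normally returns the number in each cell. If that number is then read as the number for the whole setting at one round, each arm receives half of what the stated power needs.

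Nigeria is the only country in the evaluation with a comparison group, and the Sample size section says that the evaluation was meant to be powered for small increases in mCPR. If the stated power is too high there, a true effect of the assumed size is more likely to be missed than readers are told.

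**Working it through.** **Inputs.** Prevalences come from the Sample size section and the inflation factors from Tables 4 and 5. Assumed, because not stated: two-sided alpha 0.05 and an equal split between arms.

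**1. Reproduce the targets.** n per arm per round = (z_alpha + z_beta)² × [sum of the four p(1−p)] / (difference in differences)².

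- Nasarawa: the difference is (5.1 − 3.0) − (3.1 − 3.0) = 2.0 points. The sum is 2 × 0.0291 + 0.030039 + 0.048399 = 0.136638. With z = 1.96 + 1.28 (90% power): 3.24² × 0.136638 / 0.02² = 3585.9. Table 5 has 3586.
- Ogun: the difference is (72.6 − 64.4) − (65.6 − 64.4) = 7.0 points. The sum is 2 × 0.229264 + 0.225664 + 0.198924 = 0.883116. With z = 1.96 + 0.84 (80% power): 2.80² × 0.883116 / 0.07² = 1412.99. Table 5 has 1413. At 90% power it would be 1894.

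Oromia (1132) and Mwanza (1217) reproduce as two-proportion sample sizes per round at two-sided 0.05 and 90% power. This supports the inferred alpha and the per-round reading.

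**2. Reproduce the inflation.**

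- Nasarawa: 3586 / 0.97 × 1.1 = 4067; × 1.12 = 4555.
- Ogun: 1413 / 0.15 × 1.1 = 10 362; × 1.16 = 12 020.

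Neither chain contains a factor for two arms. On the formula's own terms the per-round totals would be 2 × 4555 = 9110 and 2 × 12 020 = 24 040.

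**3. How the article uses the figures.**

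- Table 2 attaches 4555 to four LGAs and 12 020 to two.
- Husbands in Nasarawa: 4555 × 0.97 / 17 = 260, against a target of 250. With 9110 girls the interval would be 9110 × 0.97 / 250, about 1 in 35.
- Ogun EAs, at about 100 households per cluster: 710 × 100 × 0.19 × 0.90 = 12 141 girls. This is close to 12 020 and far from 24 040.
- Nasarawa EAs on the same basis: 1150 × 100 × 0.29 × 0.15 = 5003. This is only a rough check, as discussed under the objection.

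**4. Power if the figures are per-round totals.** SE = √(sum / n per cell); power = Φ(effect / SE − 1.96).

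| Estimate | Effective n per cell | SE (points) | Power |
|---|---|---|---|
| Nasarawa, pairs pooled, 2.0 points | 3586 / 2 = 1793 | 0.87 | Φ(2.29 − 1.96) = 63% |
| Nasarawa, one LGA pair, 2.0 points | 3586 / 4 = 896.5 | 1.23 | Φ(1.62 − 1.96) = 37% |
| Ogun, 7.0 points | 1413 / 2 = 706.5 | 3.54 | Φ(1.98 − 1.96) = 51% |

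With one-sided 0.05 the pooled Nasarawa figure is Φ(2.29 − 1.645) = 74%.

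**5. Detectable effects.**

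- Nasarawa at 90%: 3.24 × 0.873 = 2.8 points, or 2.9 if the variance is updated for the larger endline prevalence.
- Ogun at 80%: 2.80 × 3.536 = 9.9 points, or 9.8 with the variance updated.

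**The case against.** **The deciding text is not at hand.** The article refers to a supplementary file for sample size details and to separate country protocols. Either could say that the figures are per arm, so that the article merely lost a label. This stands, and it is why the conclusion is conditional. A reader might infer that the study was certainly planned at 63% power; the documents do not establish that. They do establish that the article cannot be right throughout, because Table 2 and the 1-in-17 interval use 4555 as a total.

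**Another formula might lie behind the targets.** Some continuity-corrected endline-only comparisons come close as two-arm totals (Nasarawa 3562, one-sided, 90%; Ogun 1424, two-sided, 80%). They need different sidedness in the two states and match neither figure exactly. Read as totals, the targets would give an endline-only comparison about 86% power in Nasarawa and 81% in Ogun. That is not the planned analysis. Under the planned one, the power in step 4 follows however 3586 was obtained.

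**The Nasarawa EA count is weak evidence.** EAs there average 44 households and whole EAs are added until 100 is reached, so three average EAs give 132 households. Then 1150 × 132 × 0.29 × 0.15 = 6603 girls, between 4555 and 9110. Counting the 1150 as single EAs gives 1150 × 44 × 0.29 × 0.15 = 2201. This criticism stands. Even 6603 girls would give 1793 × 6603 / 4555 = 2599 per cell, SE 0.73 points and about 79% power.

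**Ogun.** The interval of 7–14 for cohabiting adults decides nothing: 12 020 × 0.15 / 250 = 7.2 and 24 040 × 0.15 / 250 = 14.4 fit its two ends, and the article attributes the range to uncertainty about sexual activity. A reader might also infer that Ogun misses a stated power. None is stated, and the 80% is only what reproduces 1413.

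**Allocation of EAs.** Table 2 could be read as one draw across the whole state, leaving the arms unequal. The protocol names the study LGAs and does not describe such a draw.

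**Conclusion.** The mismatch is real. For Nasarawa, 3586 is exactly a per-arm, per-round requirement, while 4555 is presented and used as the setting total. If it is the total per round, power for the 2.0-point effect is about 63% pooled and about 37% for one LGA pair, against the stated 90%. The 90% is claimed for the state, so the pair figure contradicts no separate claim; it matters because pairs are estimated first and pooled only if similar.

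Ogun has the same mismatch: about 51% as a total, against the 80% at which 1413 reproduces.

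These figures rest on two-sided 0.05, an equal split between arms (and between pairs for the 37%), the article's own prevalences and design effects, and the full total being surveyed at each round. One-sided 0.05 raises pooled Nasarawa to about 74%. If 4555 covered both rounds together, the pooled figure would fall to about 37%. No reading of 4555 as a total reaches 90%. If 4555 is instead per arm, the power statement can stand and the sampling description is wrong.

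**What to change.** Label the Nigerian columns of Table 5 as either per arm per round or total per round, and make the rest of the article agree.

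- **If they are totals per round:** replace 90% for Nasarawa by about 63% for the pooled estimate, and state about 51% for Ogun. Give the detectable effects: about 2.8–2.9 points at 90% power for Nasarawa and 9.8–9.9 points at 80% for Ogun. State the alpha and its sidedness. This costs wording and a less favourable power figure; no more girls are needed.
- **If they are per arm per round:** correct Table 2 to 9110 and 24 040 per round, and recalculate the EA counts and the Nasarawa husband interval (about 1 in 35), which now describe about half that size. The cost is roughly double the fieldwork that the article describes, unless the country protocols already provide for it.
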